### Subgroup analyses

While recognizing the anticipated nature of these findings, subgroup analyses will be tentatively explored to uncover potential variations in outcomes based on demographic factors such as gender, age, and socioeconomic status. Although overall improvements are expected, further investigation will be warranted once the study is executed to draw more concrete conclusions from these subgroup analyses.

## Discussion

The primary objective of this study is to assess the impact of an educational intervention based on social media on the mental health literacy of high school students in Ramhormoz city. Mental health literacy, defined as knowledge and beliefs aiding in the recognition, management, or prevention of mental disorders, encompasses various components crucial for fostering good mental health and addressing mental disorders (Jorm, 2012).

Social media, being a widely used and accessible platform for communication and information sharing among young people, holds the potential to enhance mental health literacy. However, the utilization of social media for mental health education brings forth challenges and risks, including exposure to misinformation, cyberbullying, and privacy concerns (Kutcher et al., 2016). Consequently, the study emphasizes the need for tailored and evidence-based educational interventions on social media, designed to meet the specific needs and preferences of the target audience (Kutcher et al., 2016).

The intervention in this study involves a series of culturally appropriate and interactive social media posts covering a range of mental health topics. The randomized controlled trial design, comparing an intervention group to a control group, will measure mental health literacy and attitudes toward seeking professional psychological help as primary and secondary outcomes, respectively.

### Strengths of the study

*Researcher-Developed Intervention:* The study leverages a researcher-developed intervention based on the core components of the Mental Health and High School Curriculum Guide. This enhances the attractiveness and facilitates accurate comparisons with other studies utilizing the Guide.*Use of Social Media Platform:* Instead of traditional face-to-face training, the study capitalizes on the popularity of social media, particularly among students and adolescents. This approach aims to create a more engaging and flexible intervention aligned with students’ free time.*Two Three-Month Follow-Up Phases:* The study’s inclusion of two three-month follow-up phases strengthens its design by assessing the maintenance of intervention results over time.

### Challenges and limitations

*School Cooperation:* Anticipated challenges include potential non-cooperation from schools. Efforts will be focused on engaging education officials and teachers to support study referrals and enhance student engagement, rather than relying solely on lobbying and advocacy.*Student Non-Cooperation:* Non-cooperation from some students is another potential limitation. Designing educational content in an attractive way aims to mitigate this factor.*Short Follow-Up Period*: The study acknowledges the relatively short follow-up period of approximately 6 months. The hope is to demonstrate significant benefits within this timeframe, encouraging the development of mental health literacy programs.

## Conclusion

In conclusion, this study seeks to evaluate the effectiveness of a social media-based educational intervention on the mental health literacy of high school students in Ramhormoz city. Anticipating significant improvement in mental health literacy and attitudes toward seeking professional psychological help in the intervention group, the study aims to demonstrate the efficacy of using social media for mental health education. The expected positive reception from participants indicates increased knowledge, awareness, and confidence in dealing with mental health issues.

The study’s outcomes are poised to offer valuable insights for policymakers, educators, health professionals, and researchers interested in utilizing social media for mental health promotion. By showcasing the effectiveness of social media as a platform for mental health education in a resource-constrained setting, the study provides evidence-based and culturally tailored strategies. The implications extend beyond Iran, influencing the development of programs that foster positive attitudes toward mental health among adolescents in similar contexts.

Acknowledging potential challenges and limitations, the study encourages further research to address these constraints and explore sustained positive effects over an extended period.

### Trial status

This trial is still in the planning stage and has not been implemented yet. The trial protocol has been approved by the Ethics Committee of Tehran University of Medical Sciences (IR.TUMS.SPH.REC.1402.075). The trial has been registered in the Iran Randomized Clinical Trial Center (IRCT20230603058372N1 on June 5, 2023). The recruitment of participants is expected to start in June 2023 and end in July 2023. The intervention phase is expected to start in August 2023 and end in September 2023. The follow-up phase is expected to start in November 2023 and end in January 2024. The data analysis and manuscript writing are expected to start in February 2024 and end in March 2024. The anticipated date of completion of the trial is April 2024.

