**Methods:**

This randomized controlled trial (RCT) evaluated the effectiveness of a social media-based intervention, designed around the core components of *The Guide* training package. The study involves all high schools in Ramhormoz city using a stratified random sampling method. A total of 204 students are expected to participate. Measures of mental health literacy and attitudes towards seeking professional psychological help are evaluated at three time points: before the intervention (baseline), 3 months, and 6 months after the intervention.

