##### Duration and social media platforms

The intervention will span 1 month, consisting of 15 sessions. Each session will last approximately 30 min to 1 h, with 3–4 sessions delivered per week to ensure timely completion. The content will be regularly updated on Rubika and Eitaa, allowing participants to access both synchronous and asynchronous materials.

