### Data collection

In this randomized trial study, the statistical population consists of secondary school students from schools in Ramhormoz city. After coordinating with the schools and obtaining the phone numbers of the students, the link of the questionnaire that was created through Porsline website will be shared with them. The students will be asked to complete the study tool before, 3, and 6 months after the intervention.

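### The 6-month assessment falls outside the stated follow-up phase, which closes 1 to 2 months too early

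*Protocol article*

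**What the plan says.** **Assessment schedule.** The Data collection section states: "The students will be asked to complete the study tool before, 3, and 6 months after the intervention". The Methods paragraph of the Abstract gives the same times: "before the intervention (baseline), 3 months, and 6 months after the intervention". Both count from the intervention. Strengths of the study lists two follow-up phases of three months each as an advantage, and Challenges and limitations describes follow-up as lasting about six months.

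**Length of the intervention.** Under Duration and social media platforms: "The intervention will span 1 month, consisting of 15 sessions", "with 3–4 sessions delivered per week to ensure timely completion".

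**Calendar.** The Trial status section gives four dates that matter here:
- Intervention: "The intervention phase is expected to start in August 2023 and end in September 2023".
- Follow-up: "The follow-up phase is expected to start in November 2023 and end in January 2024".
- Analysis: "The data analysis and manuscript writing are expected to start in February 2024 and end in March 2024".
- Completion: "The anticipated date of completion of the trial is April 2024".

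**The concern.** The schedule and the calendar are both printed in the same article, and they cannot both be followed. An intervention that finishes in late summer or September 2023 has its six-month point in late winter or March 2024, after follow-up has closed and while the data are being analysed.

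The last assessment is one of only two follow-up times at which Data collection schedules the questionnaire, and it serves both the primary outcome (mental health literacy) and the secondary outcome (attitude to seeking professional help). The plan also relies on the contrast between the two times. It expects the attitude score to behave differently at 3 and at 6 months, and the Results section considers booster sessions because the effect is expected to fade by 6 months. A measurement taken at 4 to 5 months and labelled 6 months would not test that expectation. The claim that effects are maintained would also rest on a shorter interval than the one reported.

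**Working it through.** **Inputs, all from the protocol article.**
- Assessments at 3 and 6 months after the intervention (Abstract, Methods; Data collection).
- Intervention of one month, 15 sessions at 3 to 4 per week (Duration and social media platforms). At that pace 15 sessions take 15/4 = 3.75 to 15/3 = 5 weeks, which agrees with one month.
- Intervention August to September 2023, follow-up November 2023 to January 2024, analysis February to March 2024, completion April 2024 (Trial status).

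Exact days are not given, so I tried the range within each stated month. The earliest end is 31 August (start on 1 August plus one month) and the latest is 30 September. Follow-up is assumed to stay open to 31 January 2024, the reading kindest to the plan.

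**Formulas.** Due date = end of intervention + 3 or + 6 months. Months available = days from end of intervention to 31 January 2024, divided by 30.4375. Shortfall = 6-month due date − 31 January 2024.

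| End of intervention | 3-month date | 6-month date | Months available to 31 January | Shortfall (days) |
|---|---|---|---|---|
| 31 August 2023 | 30 November 2023 | 29 February 2024 | 153/30.4375 = 5.03 | 29 |
| 1 September 2023 | 1 December 2023 | 1 March 2024 | 4.99 | 30 |
| 15 September 2023 | 15 December 2023 | 15 March 2024 | 4.53 | 44 |
| 30 September 2023 | 30 December 2023 | 30 March 2024 | 123/30.4375 = 4.04 | 59 |

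Trial status says that the intervention phase ends in September, so on a strict reading the 6-month dates run from 1 to 30 March 2024.

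**Other readings.**
- Follow-up closing on 1 January instead of 31 January: 4.04 months available after a 31 August end, 3.06 after a 30 September end.
- Counting from the first possible day of the intervention: 1 August 2023 + 6 months = 1 February 2024, one day after the close. The schedule, however, counts from after the intervention.
- Working backwards: a 6-month assessment by 31 January 2024 needs an intervention finished by 31 July 2023, before its stated August start.

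**Spacing of the two follow-ups.** If the 3-month assessment is on time (30 November to 30 December), 62 to 32 days remain until 31 January, about 2 to 1 months. The second follow-up could then not come three months after the first.

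**Analysis.** February 2024 begins 28 days before the earliest 6-month date (29 February).

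**The case against.** **The calendar is only a projection.** Every phase date in Trial status is an expectation for a trial described as not yet implemented. The operative instruction is arguably the one in Data collection, which ties assessments to the intervention and not to calendar months. A trial team could follow that and let the dates slip. This stands as a limit: an early last assessment follows only if the calendar is obeyed. It does not remove the conflict, since the article does not say which statement prevails.

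**A reader might infer that the 6-month outcome cannot be collected at all.** The documents do not support that. The true dates, 29 February to 30 March 2024, all precede the April 2024 completion date, and the questionnaire is sent as an online link. What fails is the fit with the stated follow-up phase and the order of collection and analysis.

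**A reader might also infer that opening follow-up in November is too early for a 3-month assessment.** It is not an error. A phase can open before its first assessment falls due, and the 3-month dates (30 November to 30 December) lie inside the stated phase.

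**Planning from the start of the intervention.** Counting from 1 August misses by one day, and Challenges and limitations speaks only of about six months. This may explain how the dates arose, but it does not reconcile them with a schedule that counts from after the intervention.

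**Limited reach.** The conflict leaves randomisation, the outcome definitions, the sample size and the 3-month comparison untouched. That is correct. The effect is confined to the last time point, but it covers both outcomes there.

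**Conclusion.** The inconsistency is real. No choice of days within the stated months puts a date six months after the intervention inside the stated follow-up phase. The 6-month date falls 29 to 59 days after the close, and the calendar allows at most 5.0 months (end on 31 August) to 4.0 months (end on 30 September).

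These figures assume a one-month intervention starting no earlier than 1 August and ending no later than 30 September 2023, and follow-up open until the last day of January 2024. An earlier close in January makes the gap larger.

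The consequence depends on the calendar being followed: the last assessment of both outcomes would then come 1 to 2 months early, the two follow-ups would not be three months apart if the first is on time, and analysis would start before any 6-month questionnaire is due. This is more than a clerical slip, because it decides what interval the final results describe. It does not make the 6-month data unobtainable.

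**What to change.** Reconcile Trial status with the Abstract (Methods), Data collection, Strengths of the study, and Challenges and limitations:

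1. State that the 3- and 6-month assessments are counted from the last session.
2. Extend the follow-up phase through at least the end of March 2024.
3. Start the 6-month analysis only after the last 6-month questionnaire is in.
4. Move the completion date if needed. If the two months now given to analysis and writing are kept, they shift from February–March to April–May 2024, and completion moves from April to about June.

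A visit window around each assessment would be useful but is optional, and may already stand in the full protocol.

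If the calendar cannot move, label the last assessment by the interval actually achieved and word the maintenance claim to match.

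The cost is a delay of about two months to the analysis. No additional assessments or participants are needed, and by its own account the trial had not yet been implemented.
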